#### Lung cancer screening

Low dose computed tomography (LDCT) LCS will be conducted in the Mayo Lung Screening Program. All sites are designated as American College of Radiology (ACR) LCS centers. The parameters of the screening at each participating site are done in accordance with ACR and CMS requirements [82]. The screening is done with the patient lying in the scanner with arms overhead and accomplished in a single breath-hold in < 15 s. The CT is read by a thoracic radiologist who has received ACR accreditation and read using the Lung-RADS (lung imaging reporting and data system) standardized lung nodule reporting scheme as required by ACR [83]. The program collects and submits data to the ACR registry for each LDCT LCS performed. Every patient receives a letter with recommendations and their scan report, which are also sent to their designated practitioner. The next annual screening CT is recommended for patients with a normal scan or those with one or more nodules < 6 mm; interval follow-up is provided for nodules < 10 mm. Patients with nodule(s) ≥ 10 mm or adenopathy are referred to a pulmonologist associated with the Mayo Lung Screening Program and pursued in accordance with published guidelines using a multidisciplinary approach.

### Assessments

Assessments will occur at baseline and one, three, six, and 12 months post randomization. Follow-ups will be conducted by telephone by research staff who are not blind to treatment assignment but who do not have any role in intervention delivery. We will pilot test measures with 8–10 LCS patients (not participants) to ensure wording and administration are appropriate for older adults [84]. We expect at least 80% follow-up at 12 months based on previous research by our team [29, 85, 86] and retention of > 90% in previous Mayo Clinic LCS studies [87]. To maximize follow-up, we will: (1) provide clear information about the study at the outset, including expectations for follow-up data collection; (2) reimburse participants with graduated incentives for all follow-up data collection, including a separate incentive for CO testing at 12 months; and (3) emphasize the importance of survey completion regardless of smoking status. If follow-up rates are lower than expected, we will consider implementing additional modes of follow-up (e.g. online survey) used successfully by our team at minimal cost.

#### Baseline variables

To characterize the sample and examine moderators of treatment effectiveness, the baseline assessment will assess: demographics (age, sex, ethnicity, race, marital status, education, number of household tobacco users); perceived vulnerability and worry about lung cancer (personal risk of developing cancer, their likelihood compared to other smokers, and their level of worry about getting lung cancer); current smoking and smoking history (smoking frequency and rate, lifetime and past 30-day use of other tobacco products and e-cigarettes); motivation to quit smoking will be measured with the Readiness Ladder [88, 89] and an item regarding confidence in quitting; quitting history, including past year quit methods; nicotine dependence will be measured with the Fagerström Test for Nicotine Dependence [90].

The following metrics will be extracted from the BOSS Registry for all patients that are determined eligible for LCS: age; education; race/ethnicity; body mass index; referral source; and smoking status. We will compare patients eligible for LCS to study participants on these characteristics to evaluate representativeness of the study sample.

#### Process variables

Treatment utilization will be assessed via self-report at each follow-up and automated tracking metrics extracted from BecomeAnEX and the BOSS Registry. At each follow-up, participants will be asked about their use of any cessation methods. The following metrics will be extracted from BecomeAnEX: total time spent logged into the website; number of return visits; use of the static content and videos; use of interactive components/tools; number of replies to interactive text messages; unsubscribe rates; modal day of unsubscribe; number of days enrolled in TXT; and number of text messages received. The following metrics will be extracted from BOSS regarding completion of TTS counseling: number and duration of completed TTS counseling sessions; tobacco use status; confidence and importance for quitting or maintaining abstinence; medication use; cravings/urges and management strategies.

TTS intervention fidelity will be monitored throughout the study via review of digital audio recordings. Audio review will be conducted using a fidelity measure based on the Mayo Clinic treatment model including items adapted from the Motivational Interviewing Treatment Integrity Code [60].

#### Primary outcome

The primary outcome is biochemically confirmed (carbon monoxide [CO]) abstinence at 12 months post randomization. All participants who self-report seven-day abstinence at the 12-month follow-up will be invited to provide a breath sample for CO testing. Expired alveolar CO concentrations of ≤ 10 ppm will be considered verification of abstinence [91]. Participants who decline testing will be considered smokers.

#### Secondary outcomes

Other smoking-related outcomes will include change in motivation to quit, number of quit attempts, and 30-day and continuous abstinence measured at each follow-up [92]. Intervention satisfaction in all three arms will be measured with an adapted version of the Client Satisfaction Questionnaire [93]. We will assess overall satisfaction and perceived helpfulness, whether the intervention met their expectations (1 = not at all, 5 = very much), and whether they would recommend it to a friend (yes/no). We will include items that address usability of the WEB and TXT interventions by modifying measures from the System Usability Scale (all measures 1 = strongly disagree, 5 = strongly agree): whether they found them unnecessarily complex; whether they found them easy to use; whether they felt they would need the support of a technical person to be able to use them; whether they felt very confident using them; whether there was too much inconsistency in them; and whether they would imagine that most people would learn to use them very quickly [94]. Quality of life will be measured at baseline and 12-month follow-up with the Smoking Cessation Quality of Life Questionnaire [95, 96] and will be assessed with a single item 10-point rating scale at one-, three-, and six-month follow-ups.

#### Medical outcomes

BOSS provides the ability to capture radiology results of LDCT of patients with lung nodules such as Lung-RADS, follow-up procedures, diagnosis of lung cancer, vital status, and other concurrent diagnoses. Follow-up LCS status will be determined using data from the BOSS Registry at one year (all participants) and two years (~80% participants).

### Data monitoring

At the start of the study, a Data Safety Monitoring Committee will be established, comprising the Principal Investigators, Data Analyst, Biostatistician, Technical Lead, and Project Manager. Every two weeks the committee will review participant accrual rate, participant drop-out and the reasons for drop-out, target enrollment status, major and minor problems related to treatment assignment, and serious adverse event reports.

This is a minimal risk study for which no Data Safety Monitoring Board is needed. Standard clinical trial operating procedures for crisis management will be in place throughout the trial. Study staff will monitor and report serious adverse events.

### Power calculation

Positive (i.e. abnormal) LCS findings increase the odds of abstinence [6, 97–99]. Therefore, to be conservative in our sample size calculations, efficacy estimates for UC are based on data from patients in previous trials with negative screening results. Among patients with negative findings in the National Lung Screening Trial, one-year abstinence rates are in the range of 9.7% [100] to 12.6% [97]. In the Danish Lung Cancer Screening Trial [98], patients received < 5 min of counseling from a nurse and 30-day abstinence at one-year follow-up was 11.4% among patients with no significant LCS findings. Cox et al. [101] reported seven-day abstinence at one year of 13%. Brief counseling for smoking cessation (<3 min) yields six-month abstinence rates of 13.4% [43]. Therefore, we conservatively estimate that biochemically verified abstinence at 12 months for UC will be 10%.

Efficacy estimates for WEB + TXT are based on several converging lines of evidence: (1) two meta-analyses have reported statistically significant effects of interactive and individually tailored interventions compared to usual care or written self-help (relative risk [RR] = 1.48, 95% confidence interval [CI] = 1.11–2.78 [30]; RR = 2.10, 95% CI = 1.25–3.52 [33]; (2) a meta-analysis by Webb et al. [102] found that the use of TXT in Internet interventions had large effects on behavior change (d = 0.81, k = 4); (3) combined Internet and TXT interventions yielded six-month sustained abstinence of 17.1% in Borland et al. [103] and 12-month repeated point prevalence abstinence of 20% in Brendryen et al. [46]. Therefore, we conservatively estimate that biochemically verified abstinence at 12 months for WEB + TXT will be 16%.

Efficacy estimates for WEB + TXT + TTS are also based on several lines of evidence: (1) abstinence reported by Fiore et al. [43] for treatment duration of 31–90 min (comparable to the TTS visit that will occur before LCS) was 26.5% (95% CI = 21.5–31.4); (2) among more than 6000 patients who received TTS counseling in the NDC outpatient clinic, seven-day point prevalence abstinence at six months under intention-to-treat (ITT) analysis was 28.1% (95% CI = 27.7–30.1) [60]; (3) in a pilot study of LCS patients who completed a TTS visit before LCS, seven-day abstinence at six months (ITT) was 34% [64]; (4) previous studies of combined Internet and TTS counseling interventions have yielded quit rates (30-day point prevalence abstinence under ITT) of 21.5% [29] to 53% [69] with a strong dose-response relationship for the number of TTS sessions. Therefore, we conservatively estimate that biochemically verified abstinence at 12 months for WEB + TXT + TTS will be 24%.

For pairwise treatment comparisons, we will use the Holm–Šídák approach to account for multiple comparisons [104]. The three pairwise comparisons will be performed with two-tailed *p* values obtained which are not adjusted for multiple comparisons. These *p* values will be ranked from smallest to largest. If the smallest *p* value is > 0.0167 we will conclude that none of the comparisons is statistically significant. If the smallest *p* value is ≤ 0.0167 this comparison will be considered statistically significant and the second smallest *p* value will be evaluated. If the second smallest *p* value is > 0.025, we will conclude that the final two comparisons are not statistically significant. If the second smallest *p* value is ≤ 0.025, this comparison will be considered statistically significant and the final *p* value will be evaluated using *p* ≤ 0.05 to denote statistical significance. For our hypothesized abstinence rates, a total sample-size of 1650 (550/group) will provide statistical power ≥ 99% for the overall comparison across treatment groups and > 85% for each of the three pairwise treatment comparisons.

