#### Aim 1 (Effectiveness) analyses

The primary outcome of biochemically confirmed point-prevalence abstinence at 12 months post randomization will be analyzed using ITT. The primary analysis of the smoking outcomes will be performed using logistic regression. Separate analyses will be performed for each abstinence endpoint. For the logistic regression analyses, the dependent variable will be smoking abstinence and the independent variable will be treatment (WEB + TXT + TTS vs WEB + TXT vs UC). Study site will be included as a covariate in the primary analyses. We hypothesize that WEB + TXT + TTS will yield higher quit rates than WEB + TXT and UC and that WEB + TXT will yield higher quit rates than UC. To test these hypotheses, all pairwise comparisons of the three treatment groups will be performed. For the primary analysis of smoking abstinence outcomes, any individual who misses a visit will be classified as smoking for that assessment. This approach is used because the data are assumed to be missing not at random (MNAR). However, this approach is sensitive to differential attrition across treatment groups and tends to overestimate the precision of the estimate of the treatment effect. Therefore, to supplement primary analysis we will perform sensitivity analysis using multiple-imputation based on pattern-mixture models under the MNAR assumption (SAS/STAT version 13.2, PROC MI and PROC MIANALYZE). Multiple imputations of missing abstinence outcomes will be imputed using the logistic regression method, with the outcome adjusted by modifying the log odds ratios (OR) [105, 106]. Since the OR relating missingness to smoking is not known, we will conduct a sensitivity analysis to assess its impact on the estimate and significance of the treatment effects.

We will examine potential moderators (e.g. screening result, gender, age) by analyzing interactions between treatment and selected variables. We will examine treatment/moderator interaction term on outcomes after entering main effects. We will also explore moderators of the relationship between treatment assignment and treatment utilization.

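### The rule for the three pairwise tests is named Holm–Šídák but written with Holm–Bonferroni cut-offs, and its 0.025 second step is stricter than 5% family-wise control needs with three arms

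*Protocol article*

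**What the plan says.** The Power calculation section of the Protocol article states that "we will use the Holm–Šídák approach to account for multiple comparisons". It then writes the rule out in full, using unadjusted two-sided p values ranked from smallest to largest:

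- Step 1: if the smallest "value is > 0.0167 we will conclude that none of the comparisons is statistically significant".
- Step 2: if the second smallest p value exceeds 0.025, "we will conclude that the final two comparisons are not statistically significant".
- Step 3: the last p value is judged at "≤ 0.05 to denote statistical significance".

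The family is fixed under Aim 1 (Effectiveness) analyses, where "all pairwise comparisons of the three treatment groups will be performed". The planning rates are 10% (UC), 16% (WEB + TXT) and 24% (WEB + TXT + TTS) with 550 per arm. The stated power is at least 99% overall and above 85% for each pair.

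**The concern.** There are two separate points.

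First, the named procedure and the written cut-offs are not the same method. A smallest p value between 0.0167 and 0.01695, or a second p value between 0.025 and 0.02532, is significant under the name and not under the numbers. A decision rule for the primary outcome should have one reading.

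Second, the three hypotheses are logically linked, because equality of two pairs of arms forces equality of the third. Holm's second step guards against two true nulls remaining after a correct first rejection, and that cannot occur here. The 0.025 hurdle leaves part of the permitted 5% error unused. It can block a real second finding whose p value lies between 0.025 and 0.05.

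**Working it through.** **Inputs.** Rates of 10%, 16% and 24%, n = 550 per arm and cut-offs 0.0167/0.025/0.05, all from Power calculation. All three pairs are tested (Aim 1 analyses). Non-attenders count as smoking, so n is not reduced. Pooled two-sample z-tests stand in for the planned site-adjusted logistic regression.

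**1. Cut-offs.**
- Holm–Bonferroni, 0.05/k: 0.05/3 = 0.0167; 0.05/2 = 0.025; 0.05/1 = 0.05.
- Holm–Šídák, 1 − 0.95^(1/k): 0.01695; 0.02532; 0.05.

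The written set is Bonferroni throughout. Rounding does not explain the first value, since Šídák to four decimals is 0.0170. The second would agree with Šídák only at three decimals.

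**2. The plan's own power.** For UC vs WEB + TXT at two-sided 0.05, with mean rate 0.13:
- null SE = √(2 × 0.13 × 0.87/550) = 0.02028
- alternative SE = √((0.10 × 0.90 + 0.16 × 0.84)/550) = 0.02020
- power = Φ[(0.06 − 1.96 × 0.02028)/0.02020] = Φ(1.003) = 84.2%

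The same formula gives 91.4% for 16% vs 24% and over 99.9% for 10% vs 24%. The overall 2-df test has about 99.996%. The stated figures are reproduced to within about one point. Held at a fixed 0.025 or 0.0167, UC vs WEB + TXT would have 76.4% or 71.5%.

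**3. Why 0.05 suffices after a first rejection.** Consider the rule: smallest p at 0.05/3; if it passes, both others at 0.05.
- All three nulls true: any error requires the smallest p ≤ 0.05/3, so the error rate is at most 3 × 0.05/3 = 5%.
- Exactly two nulls true: impossible, since two equalities imply the third.
- Exactly one null true: it can be rejected only if its own p ≤ 0.05, so the error rate is at most 5%.

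This is Shaffer's modification of Holm. It rejects everything the present rule rejects.

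**4. Size, by simulation** (1,000,000 or more trials per scenario; repeat runs agree to about 0.1 point). Power for UC vs WEB + TXT:

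| UC / WEB + TXT / + TTS | Present rule | Shaffer | Source of the TTS rate |
|---|---|---|---|
| 10/16/24% | 84.2% | 84.5% | protocol planning value |
| 10/16/21.5% | 82.4% | 84.5% | lowest combined Internet and TTS rate cited in Power calculation |
| 10/16/20% | 80.2% | 84.3% | review assumption |
| 10/16/16% | 75.0% | 79.2% | review assumption |

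The simulated 84.5% lies slightly above the 84.2% of step 2 because that formula is a normal approximation. At the planning rates WEB + TXT vs WEB + TXT + TTS goes from 91.1% to 91.5%, and all three significant from 76.0% to 76.1%. The gain is small there because UC vs WEB + TXT + TTS is almost always rejected first and one of the other two nearly always passes 0.025.

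**5. Error rates.** With all arms at 10%, family-wise error is 4.3% under either rule. At 10/16/16% the single true null is rejected 3.3% of the time under the present rule and about 4.9% under Shaffer. At 16/16/24% the figures are 3.8% and 5.0%.

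**6. Effect of the name alone.** Replacing the written cut-offs by the Šídák ones changes power by at most about 0.3 points in the scenarios run. At 10/16/16%, for example, UC vs WEB + TXT moves from 75.0% to 75.2%.

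**The case against.** The strongest reply is that the written rule is a legitimate step-down test with strong 5% control, spelled out so fully that an analyst needs no guesswork. Preferring Shaffer's version is then a choice of method, since Holm can be improved in any all-pairwise setting. At the protocol's own rates the two rules reach different decisions in just under 0.5% of trials, and the larger gains need a weaker TTS arm than planned.

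Much of this stands. The explicit numbers settle which rule would be applied, and the change is an efficiency gain. What remains is that the name contradicts the numbers, and that a stricter step than necessary is applied to primary comparisons with little power to spare.

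A reader might infer more than the document supports:

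- **That the mislabelling endangers the error rate.** It does not; the written cut-offs are the stricter of the two sets.
- **That the rule undermines the stated pairwise power of above 85%.** At the planning rates the full rule gives 84.2% for the smallest contrast, the same as an unadjusted 0.05 test by the formula. The small shortfall does not come from the second step.
- **That digital beating usual care while TTS adds little is the authors' priority case.** Hypotheses 1a and 1b are listed side by side and all pairs are tested without ranking. A TTS rate of 16% would contradict Hypothesis 1a.
- **That the change has no downside.** A true null is rejected more often, though within 5%, and a published rule would be altered after recruitment began in August 2017 (Trial status).

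**Conclusion.** The point holds with modest size. The name and the cut-offs disagree, which is a plain error with almost no numerical consequence. The 0.025 second step is valid but stricter than a three-arm, all-pairwise family needs. Relaxing it gains about 0.3 points per comparison under the planning assumptions, about 2 points for UC vs WEB + TXT if the TTS arm reaches 21.5%, and about 4 points if it reaches only 20% or 16%. The last two rates are assumptions made for this review. The 21.5% is a 30-day abstinence rate from a cited study, not a 12-month biochemically verified rate. All figures assume 550 per arm and pooled z-tests. The family-wise bound itself does not depend on the rates chosen.

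**What to change.** Before any unblinded analysis, rewrite the rule in the protocol and in any analysis plan that repeats it: test the smallest of the three p values at 0.0167; if it passes, test each of the other two at 0.05; call this Shaffer's modified Holm procedure. If the sponsor prefers to keep the present rule, either name it Holm (Bonferroni) or change the cut-offs to 0.01695, 0.02532 and 0.05.

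The wording change is one or two sentences and needs no more participants or data. The Shaffer option also needs the review-board step described under Protocol amendments and, where necessary, a registry update. A dated statement that the change was made without sight of outcome data by arm would protect its credibility. Correcting the name alone leaves the decision rule as published and has no such cost.

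### The 10% usual-care rate is called conservative because it comes from scan-negative patients, but with the active rates set separately at 16% and 24% a lower control rate raises power

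*Protocol article*

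**What the plan says.** All of this is in the protocol article, section Power calculation.

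- The section opens by noting that abnormal screening findings raise the odds of abstinence. For the sake of conservatism, "efficacy estimates for UC are based on data from patients in previous trials with negative screening results".
- It cites UC-type rates of 9.7% and 12.6% (US screening trial, negative findings), 11.4% (Danish screening trial, no significant findings), 13% (a further report, seven-day abstinence at one year) and 13.4% (brief counselling, six months). It concludes: "we conservatively estimate that biochemically verified abstinence at 12 months for UC will be 10" percent.
- The active arms are set from their own evidence: "we conservatively estimate that biochemically verified abstinence at 12 months for WEB + TXT will be 16" percent, and "we conservatively estimate that biochemically verified abstinence at 12 months for WEB + TXT + TTS will be 24" percent.
- On multiplicity, "The three pairwise comparisons will be performed with two-tailed" p values, judged step-down at 0.0167, 0.025 and 0.05.
- The result: "a total sample-size of 1650 (550/group) will provide statistical power ≥ 99% for the overall comparison across treatment groups", and more than "85% for each of the three pairwise treatment comparisons".

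Elsewhere, Study recruitment and informed consent starts treatment straight after the baseline assessment. The Discussion confirms that this is before the scan. Aim 1 analyses by intention to treat and lists screening result only as a possible moderator.

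**The concern.** An assumption is conservative for power if it makes the planned effect harder to detect. A low control rate does that when the effect is a fixed ratio, because fewer events then carry the same relative effect. It does the opposite when the active rate is a fixed absolute value, because every point taken off the control rate is added to the difference. The plan writes its active rates as absolute values and never says that it holds a ratio.

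The choice also does not match the trial population. Nobody is selected on scan result, so the UC arm will contain scan-positive smokers. By the plan's own opening statement, they should push the UC rate above the scan-negative rate.

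The comparison most exposed is WEB + TXT against UC (Hypothesis 1b), which carries the case for a scalable digital programme and has the lowest planned power. If it came out null, readers would set that result against a power figure described as conservative.

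**Working it through.** **Inputs (Power calculation section).** n = 550 per arm; rates 10%, 16% and 24%; two-sided tests; step-down thresholds 0.0167 / 0.025 / 0.05. Missed visits count as smoking (Aim 1 analyses), so all 550 per arm stay in the denominator.

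**Formula (single test, pooled normal approximation).** Power = Φ{(d − 1.96·s0) / s1}, where d is the difference, s0 = √(2·p̄(1 − p̄)/n), s1 = √((p1(1 − p1) + p2(1 − p2))/n), and p̄ is the mean of the two rates.

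**Step 1: the plan's own figure.** For 10% vs 16%:

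- p̄ = 0.13, s0 = √(2 × 0.13 × 0.87 / 550) = 0.02028, so 1.96·s0 = 0.03975
- s1 = √((0.09 + 0.1344)/550) = 0.02020
- (0.06 − 0.03975)/0.02020 = 1.003, and Φ(1.003) = 84.2%

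Other two-sided methods for the same comparison give 84.5% (exact enumeration), 84.4% (unpooled), 84.6% (arcsine), 83.5% (log odds ratio) and 81.9% (continuity-corrected). Simulating the written step-down rule (1,000,000 trials) gives 84.2% for 10% vs 16%, 91.1% for 16% vs 24%, and over 99.9% for 10% vs 24%. The overall 2-df test has over 99.9%, in line with the stated 99% or more. Reaching 85% for 10% vs 16% takes 563 per arm.

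**Step 2: direction of the UC assumption.** Hold WEB + TXT at 16% and move UC over rates that the plan cites:

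| UC rate | Difference | Single test, 0.05 | Step-down rule |
|---|---|---|---|
| 9.7% | 6.3 points | 87.8% | 87.9% |
| 10% | 6.0 points | 84.2% | 84.2% |
| 11.4% | 4.6 points | 60.2% | 59.4% |
| 12.6% | 3.4 points | 36.3% | 34.7% |

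Power rises as the UC rate falls. Of the five cited UC figures only 9.7% lies below 10%; 11.4% and 12.6% are both described as scan-negative.

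**Step 3: other scales (single test, 0.05).** The planned 10% and 16% correspond to a difference of 6 points and a relative risk of 16/10 = 1.60.

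| UC rate | WEB + TXT fixed at 16% | Fixed 6-point difference | Fixed RR 1.60 |
|---|---|---|---|
| 10% | 84.2% | 84.2% | 84.2% |
| 11.4% | 60.2% | 81.0% (vs 17.4%) | 89.2% (vs 18.2%) |
| 12.6% | 36.3% | 78.4% (vs 18.6%) | 92.4% (vs 20.2%) |
| 13% | 29.2% | 77.5% (vs 19.0%) | 93.3% (vs 20.8%) |

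The low UC rate is conservative only in the last column. It is mildly favourable at a fixed difference and strongly favourable at fixed absolute rates.

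**The case against.** **The 10% may suit the actual endpoint.** The planned outcome is CO-confirmed, and decliners and missed visits count as smoking. The article does not describe its cited UC rates in those terms. Suppose, as an assumption, that those rates did not already count missing as smoking. The article expects at least 80% follow-up, so 0.8 × 11.4% = 9.1% and 0.8 × 13.4% = 10.7%, a range that contains 10%. The same factor takes the cited 20% for combined Internet and text programmes to 16%, though it takes the cited 17.1% to 13.7%. This stands as a possible defence of 10%. It is not the reason the plan gives, which is scan-negativity.

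**Holding 16% fixed moves one arm only.** The first evidence listed for WEB + TXT is two relative risks (1.48 and 2.10), so a ratio reading is open. On that reading, with RR 1.60, power improves as UC rises. This also stands. A reader might infer from the 35% figure that the trial is badly underpowered for Hypothesis 1b, but the documents do not support that, because the answer turns on a scale that they leave open. Scenarios at 13% and 13.4% are weaker still as evidence about the scan-negative choice, since neither figure is described as scan-negative.

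**84% against 85% is rounding.** Agreed. The gap is under one point by the main formula and equals 563 − 550 = 13 patients per arm. A reader might take it for an error in the sample-size calculation, but the figure reproduces within ordinary tolerance.

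**Joint power.** A reader might also set the 76% chance of winning all three comparisons against the plan's claim. The plan claims power for each comparison separately and sets no all-three success criterion, so there is no contradiction.

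**Conclusion.** The point holds for the direction of the UC assumption. With the active rates stated as separate absolute values, taking UC from scan-negative patients raises power, and it also describes a narrower group than the one randomised and analysed. The word conservative is therefore wrong for the reason given. By contrast, the 16% and 24% sit below most of the rates cited for those arms, so caution there runs the right way.

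The size depends on what is held fixed. For UC between 11.4% and 12.6%, power for WEB + TXT vs UC is 59% to 35% with WEB + TXT at 16% (step-down rule), about 81% to 78% at a fixed 6-point difference, and about 89% to 92% at RR 1.60 (both single test at 0.05). These figures use the cited UC rates without any discount for CO confirmation or missing data.

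The stated pairwise power is slightly too high for the weakest comparison (about 84%). That is a minor wording matter. Nothing here shows that the sample size is wrong.

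**What to change.** In the Power calculation section, with no change to sample size, design or analysis:

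1. Restate pairwise power under the step-down rule as about 84% (WEB + TXT vs UC), 91% (WEB + TXT + TTS vs WEB + TXT) and over 99% (WEB + TXT + TTS vs UC).
2. Remove the claim that the scan-negative UC rate is conservative, or justify 10% on other grounds, such as CO confirmation and counting missing as smoking. If the second, apply the same reasoning to the active rates.
3. Add a short table of power for WEB + TXT vs UC, with UC from 10% to about 13%, under fixed absolute rates, a fixed difference and a fixed relative risk, and say which scale the planning assumes.

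The cost is a few sentences and one small table. The drawback is that the stated power looks less favourable.
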